#### Data collection of events

For all CNS residents, we will also collect historical data related to falls, dehydration, and pulmonary aspiration events retrospectively from medical and nursing charts within the period of the study and for the same period the year before.

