## Methods

### Study setting

Participants will be recruited from Campus Neurológico Sénior (CNS), a neurological nursing home, located in Torres Vedras, Portugal, which has an outpatient clinic and a residential unit for short or long-term admissions of neurologic patients or individuals aged over 65 years. CNS places its focus on comprehensive care to patients, implemented by a multidisciplinary healthcare team that includes physicians, nurses, a rehabilitation team, dieticians, psychologists, and medical assistants.

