### Eligibility criteria

All patients from the CNS residential unit (*n* = 78) who fulfil the following inclusion criteria will be invited to participate:Men or women residing at the CNS nursing home for long-term care;Risk of falling and/or dysphagia and/or dehydration defined by brief screening assessment;Willing to participate in the study;Willing to provide written informed consent;Willing to comply with the monthly required interviews.

Exclusion criteria include the presence of significant active psychiatric problems (e.g., hallucinations, confusion, psychosis) that, according to the clinical judgement of the CNS multidisciplinary team, could be aggravated with the use of risk reminders.

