#### Secondary outcomes

The secondary outcomes will be to evaluate the following:Patients’ and health professionals’ satisfaction;The efficacy of risk prompt displays in reducing the number of falls, pulmonary aspiration, and dehydration events;The type and frequency of adverse events that arise from using the risk prompt displays (for example, physical or social discomfort, skin irritability, stress, or anxiety).

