### Statistical analysis

Statistical analysis will be performed using SPSS® version 21.0; SPSS Inc. Chicago, IL [28]. Data will be described using descriptive statistics, i.e., means, medians and relative frequencies (i.e., outcome per number of days of hospitalization).

As this is an exploratory study with no previous studies having been conducted, we defined 20 patients as enough to conclude on the primary outcome on feasibility. This is a compromise between the capability to respond to a specific question and a realistic perspective of recruitment capacity using just one nursing home [29].

As our primary outcome, we will measure patients’ adherence to the risk prompts through the number of times and reasons they remove the risk prompts or refuse to use prompts during the period of the study and/or withdrawing from the study.

The secondary outcomes will be the following:Patients’ satisfaction with the risk prompt displays measured on a 7-point Likert scale and open-ended questions.Healthcare professionals’ satisfaction with the risk prompt displays as measured on a 7-point Likert scale and open-ended questions regarding the overall benefits of using the displays and overall perception of its impact on decreasing risk.Historical comparison of medical and nursing charts data on the relative frequency of number of events per number of days of hospitalization registered during the period of the study, with the same period the year before.Type and frequency of adverse events recorded during the period of the study.

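### The before/after event comparison does not separate short- from long-stay residents, so a change in stay mix between the two years could move the event rate with no effect of the prompts

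*Protocol article*

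**What the plan says.** Four parts of the protocol article bear on this.

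- **Study setting.** The centre has "a residential unit for short or long-term admissions of neurologic patients or individuals aged over 65 years".
- **Eligibility criteria.** The first inclusion criterion is "Men or women residing at the CNS nursing home for long-term care". Short-stay residents therefore cannot be participants and get no prompts within the study.
- **Data collection of events.** The chart extraction is wider than the study population: "For all CNS residents, we will also collect historical data related to falls, dehydration, and pulmonary aspiration events". It is made "within the period of the study and for the same period the year before".
- **Statistical analysis.** The measure is events per day of stay while the study runs, compared "with the same period the year before". No restriction, stratification or adjustment by stay type is mentioned, and the section does not say which of the extracted residents enter the comparison.

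Under Secondary outcomes, the objective that this comparison serves is "The efficacy of risk prompt displays in reducing the number of falls, pulmonary aspiration, and dehydration events". The Discussion explains the wide extraction: the teaching session and the monthly newsletter may lead staff to record more events, so data are taken from all residents and from the year before. It does not mention stay mix.

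**The concern.** Dividing by days of stay corrects for how many days were observed, not for whose days they were. In a mixed unit the crude rate is a weighted average of a short-stay and a long-stay rate, weighted by each group's share of days. Matching the calendar period deals with season but does not hold those weights fixed. If the weights differ between the two years and the two rates differ, the crude rate changes although nobody's risk has changed.

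This is separate from dilution. Including residents who wear no prompt pulls a real effect towards no difference. A change in stay mix can produce a difference in either direction where there is no effect at all.

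At stake is how the historical comparison is read. The protocol attaches it to an efficacy objective and says that the results will help to plan later studies, including studies of efficacy. A ratio that partly reflects admissions could be carried into that planning.

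**Working it through.** **Plan's own figure.** None exists for this comparison. The 20 patients in Statistical analysis were set by judgement for the feasibility outcome, and nothing below depends on how they were chosen.

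**Inputs from the protocol.** A mixed short- and long-stay unit (Study setting); prompts for long-term residents only and 78 patients in the unit (Eligibility criteria); all residents extracted in both periods (Data collection of events); events per day of stay (Statistical analysis).

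**Inputs that must be assumed.** Let s0 and s1 be the short-stay share of resident-days in the prior year and in the study period, and k the short-stay event rate divided by the long-stay rate. The documents give none of these.

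**Formula.** With no prompt effect and stable rates within each stay type, the ratio of study period to prior year is

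RR = [(1 − s1) + s1·k] / [(1 − s0) + s0·k].

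**Share rising from 20% to 35%:**

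| k | Numerator 0.65 + 0.35k | Denominator 0.80 + 0.20k | RR | RR if the shift is reversed |
|---|---|---|---|---|
| 1.5 | 1.175 | 1.10 | 1.07 | 0.94 |
| 2 | 1.35 | 1.20 | 1.125 | 0.89 |
| 3 | 1.70 | 1.40 | 1.21 | 0.82 |

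**Other values:**
- k = 2, share falling from 30% to 20%: 1.20/1.30 = 0.92.
- k = 0.5 (short-stay rate lower), share rising from 20% to 40%: 0.80/0.90 = 0.89.
- k = 1, any shift: 1.00.
- s1 = s0, any k: 1.00.

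Both conditions are therefore needed: a rate difference and a change in share.

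**Comparison with a real effect.** Suppose 20 of 78 residents wear prompts, with equal rates and equal days, and the prompts cut events in wearers by 30%. The all-resident ratio is then 1 − (20/78) × 0.30 = 0.92. This equals the artefact from the 30% to 20% shift at k = 2. Under these assumptions the two could not be told apart in a pooled rate.

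**If participants were set against all prior-year residents.** The analysis section does not rule this out. With no effect the ratio is 1/[(1 − s0) + s0·k]; at k = 2 and s0 = 20% that is 1/1.20 = 0.83, with no shift in mix at all.

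**After separating stay types.** Among long-term residents in both periods s1 = s0 = 0, so RR = 1.00 under no effect whatever the unit's stay mix, provided the long-stay rate is itself stable.

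**The case against.** The strongest reply is that the all-resident sentence concerns data collection. It fixes which charts are extracted, not which residents are analysed. The analysis section leaves that open, and an analysis plan that is not shown could subset by stay type from the same charts. This stands in part: a reader might infer that the plan commits to pooling everyone, and the text does not go that far. What it does fix is an all-resident extraction, justified in the Discussion as the way to handle increased registration, and a single rate per day of stay with no stay type named.

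Second, the wide extraction has a purpose. Residents who never wear a prompt but are charted by the same trained staff can show whether recording has increased. That stands, and any fix should keep it.

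Third, a reader might infer that the comparator is a different population from the treated group. If all residents are used in both periods, the definition is the same in each; what remains is drift in composition, plus dilution. Event data on residents without prompts are also collected during the study period, so the prior year is not the only available reference.

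Fourth, no figure in the documents shows that short-stay residents have a different event rate or that their share changed. A reader might infer that a change in admissions would be reported as benefit or harm; the documents support only that it could be.

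Finally, the outcome is secondary and descriptive, with no test or decision rule, in a feasibility study of 20 patients. That limits the consequence but does not remove the problem.

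**Conclusion.** The concern holds in a limited form. The unit is mixed, the prompts are limited to long-term residents, events are extracted for all residents in both periods, and the stated rate does not distinguish stay types. A crude before/after ratio can therefore differ from 1 with no prompt effect.

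The bias requires both a difference in event rate by stay type and a change in the short-stay share of days. Neither is documented, so its size and direction are unknown. The illustrative 1.07 to 1.21, or 0.94 to 0.82 in reverse, rests on an assumed shift between 20% and 35% and an assumed rate 1.5 to 3 times as high. The documents do not support the stronger conclusion that the comparison is biased, or biased in a particular direction. The primary adherence outcome is untouched. The change is worth making because it is cheap and also reduces dilution.

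**What to change.** Keep the all-resident chart extraction as it is. In Statistical analysis, state that the main historical comparison is events per day of stay among all long-term residents, participants and non-participants, in both periods. Report short-stay residents for both periods on a separate line.

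The separate line also serves the concern raised in the Discussion: a rise among residents who never had a prompt, charted by the same staff, would point towards more registration. Pooling hides that signal.

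A table of long-term residents present in both periods, each with their own two rates, is optional and descriptive only. Those residents are a year older in the study period and are selected for survival and continued stay.

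The cost is one filter by stay type on charts already being extracted, and fewer resident-days in the main comparison. The filter does not remove turnover or changing risk among long-term residents. Nor does it reproduce the trial's eligibility, which also requires screened risk and consent.

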### Outcomes

#### Primary outcome

To evaluate the feasibility of risk prompt displays designed to communicate risks.

#### Secondary outcomes

The secondary outcomes will be to evaluate the following:Patients’ and health professionals’ satisfaction;The efficacy of risk prompt displays in reducing the number of falls, pulmonary aspiration, and dehydration events;The type and frequency of adverse events that arise from using the risk prompt displays (for example, physical or social discomfort, skin irritability, stress, or anxiety).

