## Background

Due to demographic ageing and increased life expectancy, an increasing number of elderly spend the end of their life in an institutional setting [1].

Nursing homes provide 24-h nursing care to residents with heterogeneous diagnoses, different degrees of functional status, and complex care needs [2]. Falls, pulmonary aspiration, and dehydration are a particular problem in nursing homes and a major contribution to the deterioration of independence and quality of life of residents [2–7].

The incidence of falls and fall-related injuries, which is a major external cause of death in those living in healthcare institutions, has been reported in numerous epidemiologic studies [8–10]. Choking and aspiration pneumonia are also frequent; choking is the most common external cause of death in residents under 65 years old, while aspiration pneumonia is particularly difficult to diagnose since the moment of aspiration is usually not observed [8–11]. Dehydration, due to poor fluid intake or pathologic loss of body fluids, is considered to be present in 0.8 to 1.4% of nursing home residents. It is associated with frailty, poor cognition, falls, delirium, disability, and mortality and is a major cause of decreased attention and fluctuating mental status, the hallmarks of delirium, in the nursing home [12].

To provide high-quality care and prevent these risks, nursing home multidisciplinary team members (i.e., physicians, nurses, professionals from rehabilitation team, psychologists, social workers, and medical assistants) need to work as a coordinated team, have an effective system of communication with access to information, and understand the residents’ needs [13, 14].

The use of risk prompt displays by nursing home patients may improve the access to information and communication between healthcare professionals, which may in turn reduce the number of falls, dehydration, and pulmonary aspiration events. As soon as a patient is admitted, the nursing team would be responsible for screening for falls, dehydration and pulmonary aspiration risks, and for suggesting the corresponding risk prompt displays that should be used. The local multidisciplinary team would validate the nursing team’s suggestions before a patient would start using the risk displays in their daily routine in the nursing home.

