The aim of this study is to develop and evaluate the feasibility of a set of risk prompt displays to communicate the risk of falls, dehydration, and pulmonary aspiration and to reflect on tailored interventions that would appropriately manage these events in nursing homes. In order to do this, a national, single-center, feasibility study will be conducted. The duration of the study for each participant will be a minimum of 3 months.

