## Discussion

Thoughtful selection of proper risk prompt displays in nursing homes is an essential step along a path toward efficient communication of risks among teams. We expect that the displays will potentially improve communication given their simplicity, discretion, low complexity, and minimal physical requirements.

The results of the study will enable the planning, at a later stage, of clinical studies designed to respond to more pragmatic questions regarding the use of risk prompt displays, such as (1) efficacy of the use of the risk prompt displays, (2) better clinical trial design to evaluate the efficacy of displays, including outcomes, (3) a better treatment strategy including the combination of non-pharmacological therapies with the use of the risk prompt displays, and 4) introduction of the use of a risk prompt bracelet in the therapeutic areas studied.

A limitation of this study is that the teaching session or the monthly reports encourage event registration, resulting in an apparent increase of events during the period of the study. For that reason, we will widen data collection to all CNS residents, and will also collect data of events in the same period, 1 year before.

This study will only be conducted in one nursing home, which could be a limitation. However, the CNS population is representative in age, heterogeneity of diagnosis, and symptoms of other nursing homes. As this is a protocol for a first exploratory study, we anticipate that running the study in just one nursing home will not compromise the capability to conclude on patients’ adherence.

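### Efficacy against falls, aspiration and dehydration is listed as an outcome, but the design leaves efficacy to later studies and can only describe event rates

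*Protocol article*

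**What the plan says.** The Protocol article's Secondary outcomes section lists, as something this study will evaluate, "The efficacy of risk prompt displays in reducing the number of falls, pulmonary aspiration, and dehydration events".

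Three other places bear on that outcome:

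- **Statistical analysis.** The sample size statement is "we defined 20 patients as enough to conclude on the primary outcome on feasibility". No figure is offered for the event outcomes. The general method is "Data will be described using descriptive statistics, i.e., means, medians and relative frequencies", the last being outcomes per day of stay. The efficacy outcome becomes a chart-based comparison of event frequency per day of stay between the study period and the corresponding period one year earlier.
- **Data collection of events.** The comparison covers the whole home: "For all CNS residents, we will also collect historical data related to falls, dehydration, and pulmonary aspiration events".
- **Discussion.** "The results of the study will enable the planning, at a later stage, of clinical studies", and efficacy of the displays is the first question named for those studies. The same section concedes that the teaching session and monthly reports may raise the number of events recorded.

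The only event frequency in the article is in the Background, where dehydration "is considered to be present in 0.8 to 1.4% of nursing home residents". No rate is given for falls or aspiration.

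**The concern.** The outcome list and the Discussion assign efficacy to different studies. The design fits the Discussion: there is no concurrent control, the size was chosen for feasibility, and the analysis sets two crude rates side by side. Labelling that contrast efficacy promises more than it can deliver.

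Two features make the label risky. Crude events per day do not distinguish one resident with ten falls from ten residents with one fall each. For a rare event, a change of one or two episodes looks like a large relative change. If the results are reported under the heading in the outcome list, a reader could take a small or chance difference as evidence that the displays work or do not work. The later trial would also be planned on rates whose uncertainty is not shown.

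**Working it through.** **The plan's own figure.** The 20 patients cannot be reproduced, because no error rate, power, effect or precision target is given. The number is justified for feasibility and by recruitment capacity, so there is no sizing of the event comparison to check.

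**Inputs from the article.** 78 residents (Eligibility criteria, read as the whole residential unit); dehydration prevalence 0.8 to 1.4% (Background); at least three months of follow-up per participant, taken as 90 days; events collected for all residents in both periods.

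**Assumptions that are not in the article.** Full occupancy and equal resident-days in the two periods; 4 to 8 falls per 1000 resident-days; variance doubled to represent repeat fallers; a halving of the rate as the illustrative effect.

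**Dehydration**

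1. Expected number dehydrated at one time: 78 × 0.008 = 0.62 and 78 × 0.014 = 1.09.
2. This is a prevalence, so the number of episodes over three months may be higher. As a stress test, take four times the upper figure: 4 × 1.09 = about 4.4 episodes in the earlier period.
3. If *b* episodes in the earlier period fall to none, the exact conditional 95% interval for the rate ratio runs from 0 to 0.025^(−1/*b*) − 1:
   - *b* = 1: 40 − 1 = 39
   - *b* = 4: 40^(1/4) − 1 = 1.51
   - *b* = 5: 40^(1/5) − 1 = 1.09
   - *b* = 6: 40^(1/6) − 1 = 0.85

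   At least six episodes falling to none are therefore needed before the interval excludes 1.
4. Power of the exact conditional test (two-sided 0.05) to show a halving is below 0.1% with 0.62 to 1.09 expected earlier episodes, and about 5% with 4.4.
5. For 80% power the approximate requirement is (1.96 + 0.84)² × (1 + 1/0.5) / (ln 0.5)² = about 49 earlier-period episodes.

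**Falls**

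1. Resident-days per period: 78 × 90 = 7020.
2. Falls per period: 7020 × 4/1000 = 28 and 7020 × 8/1000 = 56.
3. The 95% interval factor for a rate ratio with *d* events in each period is exp(1.96 × √(2/*d*)):
   - *d* = 28.1: exp(0.523) = 1.69
   - *d* = 56.2: exp(0.370) = 1.45
4. With variance doubled, exp(1.96 × √(4/*d*)):
   - *d* = 28.1: exp(0.740) = 2.10
   - *d* = 56.2: exp(0.523) = 1.69
5. Dilution. The comparison covers all residents, but only participants use the displays. If 20 of the 78 did so (assumption), with the same fall rate as the rest, halving their falls would give a whole-home ratio of 1 − 0.5 × 20/78 = 0.87. Even the narrowest interval around no change, 1/1.45 = 0.69 to 1.45, contains that value.

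**Aspiration.** The article gives no rate, and none is assumed here.

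**The case against.** The strongest defence is that this is a secondary outcome of a study that calls itself exploratory. No power is claimed for it, and no efficacy conclusion is promised. A first look at event rates followed by proper efficacy studies is a normal sequence, and the Statistical analysis section already turns the outcome into a descriptive historical comparison. Intervals and models are also what an article may leave to a fuller plan. Much of this stands: the sample size is not wrong, and the mere absence of a model is not the point. What remains is that the outcome is named as efficacy in reducing events, while the same article gives that question to later studies. A fuller analysis plan would not remove that conflict in the stated objectives.

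Three stronger readings are tempting, and the article does not support them:

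- **That the study period will often contain no dehydration at all.** With 78 residents the prevalence gives a 33 to 53% chance that nobody is dehydrated, but only at a single moment. The outcome counts events over at least three months in a neurological home, and the prevalence is for nursing homes in general.
- **That falls would be compared in 20 participants only.** This would give intervals of ×/÷2.1 to 2.8 at the same assumed rates. The article collects events for all residents, so those intervals are too wide for the planned comparison. Falls may prove frequent enough for a usable interval.
- **That a fall in events is bound to be reported as benefit.** The article expects better registration to push recorded events upwards, so the bias it discloses runs the other way. An interval would not correct it.

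**Conclusion.** The point holds as one of wording and reporting. The efficacy outcome conflicts with the Discussion, and an uncontrolled before/after contrast of crude rates that may be distorted by better registration cannot support it.

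For dehydration, the article's figure implies about 0.6 to 1.1 affected residents at any one time, and a comparison stays uninformative at about four times that number. For falls, the interval of ×/÷1.45 to 1.69, or ×/÷1.69 to 2.10 with doubled variance, rests wholly on the assumed rate, full occupancy and 90 days. Since "The duration of the study for each participant will be a minimum of 3 months", longer observation would narrow it. The interval reflects chance only. The lack of a control and the change in registration would remain however many events were recorded.

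**What to change.** 1. Reword the outcome in the Secondary outcomes section: describe event rates in the study period and in the corresponding period one year earlier, to inform a later trial, with no efficacy conclusion. This brings it into line with the Discussion.
2. For falls and aspiration in all residents, report rate ratios with 95% intervals that allow for repeat events within a resident. A Poisson GEE or a negative binomial model clustered on resident, with log resident-days as offset, would serve.
3. Report the proportion of residents with at least one event in each period.
4. State beside the results that the intervals do not correct for changed registration.
5. If dehydration episodes are few, list them or give exact intervals, without a comparative claim.

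The cost is a change of wording and a small amount of extra analysis on event data already being collected, provided the charts identify the resident and days of stay for each event. The claim becomes less favourable.
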